##### Parent reports

**Vineland Adaptive Behavior Scales II (VABS-2)**

The VABS [57] is a widely-used parent interview measuring adaptive behaviour, recommended as a test-retest measure in autism treatment studies [58] and normed for all ages [59]. Items are categorised into four primary domains: communication, daily living skills, socialisation, and motor skills, with maladaptive behaviour (internalising and externalising) also examined. The VABS is administered at baseline and post-intervention; changes in mean scores across time between the intervention and control groups will be used to assess treatment efficacy. Similarly to our use of the MSEL, the baseline scores will characterise for whom the treatment is effective.

**Parenting Stress Index IV (PSI-4)**

The PSI [60] is a 120-item parent-report questionnaire assessing the extent of stress in the parent-child dyad, with foci on three core domains of stress: child characteristics, parent characteristics, and situational/demographic life stress. Mean differences in scores collected at baseline and post-intervention will be compared between the intervention and control groups.

**Family Quality of Life Survey (FQoL)**

The FQoL [61] is a 25-item parent-report questionnaire assessing perceived satisfaction in terms of quality of family life. Five domains are assessed: family interaction, parenting, emotional well-being, physical/material well-being, and disability-related support. Mean differences in scores collected at baseline and post-intervention will be compared between the intervention and control groups.

**Autism Impact Measure (AIM)**

The AIM [62] is a 25-item parent-report questionnaire that measures changes in core autism symptoms, and which has strong test-retest and cross-informant reliability [62]. Mean differences in scores collected at baseline and post-intervention will be compared between the intervention and control groups.

**Internal iPad data**

The iPad will record the child’s real-time finger movements when they are using Point OutWords, for the duration of the intervention period [30]. Changes in manual motor skills will be measured by the following parameters: (1) visuomotor targeting error is measured as the Euclidean (straight-line) distance between the initial point of contact with the screen and the nearest extent of the target puzzle piece, or the centre of the target key if in Type mode, (2) time of release and position of release relative to target are recorded, (3) motor efficiency is measured as variance of linear speed in the direction of motion, and variance of angular speed (the rate of change in direction of motion over time), (4) accuracy in movement will be measured as a ratio of the actual drag path to the shortest possible path length, and (5) the number of failed attempts to drag puzzle pieces and the overall time taken to successfully complete a piece are also recorded.

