### Intervention

Point OutWords [30] is an iPad game developed to train fine motor and cognitive skills in children with autism. Participants in the experimental group will receive the Point OutWords intervention, with a target of at least 20 h of contact time, as an adjunct to standard NHS clinical therapy. The intervention will be administered by parents/caregivers in the home, either on a loaned iPad or on the family’s own iPad if preferred. Parents will receive training from the research team to use Point OutWords, and written instructions.

Point OutWords has three modes of increasing difficulty, which tap skills prerequisite to language and communication. Learning starts in the Point mode where the child uses their finger to drag jigsaw pieces to complete a picture. The object is segmented into jigsaw puzzle pieces, which are scattered round the touchscreen. Puzzles are images from daily life e.g. bath, shampoo. The child has the opportunity to develop the manual motor skills prerequisite to pointing to interact with a touchscreen. The touchscreen software interface is adapted so as to accommodate the autistic user’s open-loop style of visuomotor control and is customisable to meet the child’s motor ability.

From here, the child progresses to Type mode. In Type mode, puzzle pieces cannot be dragged into place in an iconic style of reference, but instead must be cued by symbolic reference: Each puzzle piece is labelled with a letter in the word, there are as many puzzle pieces as there are letters in the word, and in order to cause a piece to snap into place within the puzzle, the participant must press the corresponding letter key on a virtual keyboard that appears on the touchscreen. The Type mode aims to encourage symbolic representation, with which non-verbal children with autism show difficulty [34] and which underpins communication development [35]. In addition to improving motor skills, Point OutWords teaches sequencing through piecing several parts of a puzzle together. Cognitive sequencing underlies language development along with planning for social interaction and daily activities [26].

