Finally, in the Speak mode the child assembles each jigsaw piece by speaking each syllable of a word in order, allowing the child to practise their oral motor skills. The object is segmented into a number of puzzle pieces equal to the number of syllables in the word. Each syllable is modelled, the client is prompted to speak each one, and OpenEARS speech recognition software is used to detect these pronunciations. Speaking a syllable causes the corresponding puzzle piece to snap into place. Tolerance for articulation errors and other slight inaccuracies of the match between actual and modelled pronunciations can be configured by the caregiver. Advancing to Speak mode will be difficult for the majority of children in this non-verbal/minimally verbal sample; we expect that most children will stop with Type mode.

Point OutWords is intended to be used with a parent or other caregiver who can support the child in an “errorless learning” format, filling in responses and correcting errors when the child is unable to do so independently, and redirecting the child towards the task when attention wanders. Progressing to a more difficult level is at the discretion of the caregiver in interaction with the child.

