### Statistical analysis plan

Results will be analysed by the intention-to-treat principle. Guidelines and standard practices for each outcome measure will be used to impute values for missing items in individual datasets. For example, guidelines for the SRS-2 recommend using the median of the items answered. Any systematically missing subscales within feasibility candidate measures will inform the decision as to which measures would be carried forward to a full-scale RCT. This feasibility trial aims to determine the sample size for the full RCT. Test-retest variances in internal iPad data and external outcome measures will be entered into a standard calculation of statistical power to inform the sample size of a full RCT. Participant flow in terms of recruitment and retention, reported in line with the Consolidated Standards of Reporting Trials (CONSORT) statement for non-pharmacological interventions, will also inform the sample size for a large RCT. The trial statistician will perform the power and sample size calculations. Statistical analysis will be conducted in R.

We will explore the predictability of treatment effects based on the baseline measures. Findings may shed light on whether the intervention is more suited to certain profiles of autism than others. Inclusion criteria for a subsequent full trial would be fixed accordingly. Standardised scores from psychometric assessments will be analysed using mixed-model analysis of variance with time point (pre-intervention, post-intervention) as the within-subjects factor, and treatment (intervention, control) as the between-subjects factor. The internally logged outcome measures of visuomotor accuracy in Point OutWords will be analysed using three separate exploratory analyses of covariance, with Point OutWords usage time, number of distinct Point OutWords sessions, and real time as covariates. Participants’ own responses will be discriminated from caregivers’ model inputs by a statistical clustering method. Fidelity will be assayed using descriptive reports of content, and duration and number of intervention sessions completed.

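### In Type mode, targeting error is measured to the centre of the target key, so a well-aimed press on a wrong letter counts as a large motor error and symbolic key choice is mixed with aim

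*Protocol article*

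**What the plan says.** The Internal iPad data section under Secondary outcomes introduces its list with "Changes in manual motor skills will be measured by the following parameters". The first item reads: "visuomotor targeting error is measured as the Euclidean (straight-line) distance between the initial point of contact with the screen". In Point mode the other end of that distance is the closest edge of the piece. For Type mode the text gives instead: "or the centre of the target key if in Type mode". No condition is placed on which key the child actually touched.

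The Intervention section describes the Type-mode task. Each piece carries a letter, and to place it "the participant must press the corresponding letter key on a virtual keyboard that appears on the touchscreen". The section also states the purpose: "The Type mode aims to encourage symbolic representation, with which non-verbal children with autism show difficulty". On how far children will progress, "we expect that most children will stop with Type mode".

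The Statistical analysis plan section says: "The internally logged outcome measures of visuomotor accuracy in Point OutWords will be analysed using three separate exploratory analyses of covariance". The covariates are usage time, number of sessions and real time. The only filter on logged responses is: "Participants’ own responses will be discriminated from caregivers’ model inputs by a statistical clustering method". The same section enters the test-retest variances of the internal iPad data into the power calculation for the full trial.

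**The concern.** A press in Type mode has two parts: choosing a key, then hitting it. The first is the symbolic skill that the mode is meant to teach. The second is the motor skill that the parameter is meant to measure. Distance to the required key adds the two together. A press in the exact centre of a wrong letter can score several key widths of error, while a sloppy press on the right letter scores a fraction of one.

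Two uses of the measure are exposed. First, key choice would be expected to improve along the same axes as the planned covariates, so symbolic learning could be read as a motor learning curve. Second, differences in wrong-letter rate between children and occasions add variance that has nothing to do with aim, and that variance goes into sizing the next trial. The mixing happens inside Type mode, so a term separating Point from Type mode would not remove it.

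**Working it through.** **Plan's own figure.** The protocol gives none on this point: no wrong-letter rate, keyboard layout or aim scatter. The figures below illustrate the mechanism and are not estimates for this trial.

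**Assumptions.** QWERTY layout, unit = one key width; aim scatter normal with SD 0.3 per axis; proportion *p* of presses directed at a wrong letter. The words *bath* and *shampoo* are the protocol's own puzzle examples.

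**Step 1, true aim error.** Mean distance from the key aimed at = 0.3 × √(π/2) = 0.376.

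**Step 2, score of a wrong-letter press.**
- Wrong letters spread evenly over the other 25 keys: mean centre-to-centre distance is 3.13 for *bath* and 3.89 for *shampoo*; average 3.51.
- Wrong letters only on adjacent keys: about 1.05.

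**Step 3, recorded error** = (1 − *p*) × 0.376 + *p* × (wrong-letter distance).

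| Wrong letters | Even spread | Adjacent keys |
|---|---|---|
| 30% | 0.7 × 0.376 + 0.3 × 3.51 = 1.316 | 0.7 × 0.376 + 0.3 × 1.05 = 0.578 |
| 10% | 0.9 × 0.376 + 0.1 × 3.51 = 0.689 | 0.9 × 0.376 + 0.1 × 1.05 = 0.443 |
| Fall, aim unchanged | 1 − 0.689/1.316 = 48% | 1 − 0.443/0.578 = 23% |

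Simulating the scatter around the wrong key as well leaves the even-spread figure at about 48% and moves the adjacent-key figure to about 24%.

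**Step 4, lower error rates.** Even spread, 5% falling to 2%: 0.95 × 0.376 + 0.05 × 3.51 = 0.533, and 0.98 × 0.376 + 0.02 × 3.51 = 0.439, a fall of 18%.

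**Step 5, other scatters.** A separate simulation over all 26 letters, even spread, with wrong letters falling from 50% to 10%:
- SD 0.15: 1.81 to 0.51, a fall of 72%
- SD 0.25: 1.85 to 0.62, a fall of 66%
- SD 0.40: 1.95 to 0.80, a fall of 59%

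Distance to the key aimed at stayed constant at 0.19, 0.31 and 0.50 respectively.

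**Step 6, effect on variance.** One percentage point of wrong letters shifts the recorded mean by (3.51 − 0.376)/100 = 0.031 key widths, or 8% of the true aim error, under even spread. Under adjacent spread the shift is (1.05 − 0.376)/100 = 0.007, or 2%. Any change in a child's wrong-letter rate between occasions therefore enters the test-retest variance directly.

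**Step 7, keeping only presses on or next to the required key.** Take five adjacent keys out of 25 as an assumption, with even spread and stray aim ignored.
- At 10% wrong, the retained wrong share is 0.1 × 5/25 = 0.02: (0.9 × 0.376 + 0.02 × 1.05)/0.92 = 0.391.
- At 30% wrong, the share is 0.06: (0.7 × 0.376 + 0.06 × 1.05)/0.76 = 0.429.
- The spurious fall is 1 − 0.391/0.429 = 9%, against 48% before.

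The restricted measure still responds to aim: at 10% wrong letters it goes from about 0.39 to about 0.72 as scatter doubles from SD 0.3 to 0.6. If all wrong letters are on adjacent keys, the restriction removes almost nothing and the fall stays near 23%.

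**Step 8, distance to the nearest key.** Touches landing at random over a square key average 0.383 from its centre, against 0.376 for the aim assumed in step 1. This measure could barely tell random touching from that aim.

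**The case against.** **The term is undefined.** The protocol never says that the target key is the required one, and the Intervention section states no order for placing pieces in Type mode. If any unplaced piece's letter is accepted, there is no single required key. A fuller protocol or the software description may settle this. That stands as a reason to define the term. It does not remove the point: the Intervention section supports the required-letter reading, and nothing in the article supports scoring against the key the child intended or the nearest key.

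**Wrong presses may be rare.** Pieces display their letters, so the child matches rather than spells, and caregivers fill in and correct responses under errorless learning. This may hold the rate down, and the size is open for that reason. A matching error is still not a motor error.

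**The consequences are limited.** This stands. A reader might infer that the treatment comparison is biased, but finger movements are recorded only during Point OutWords use, so the measure does not enter a between-arm comparison. A reader might infer that this is the trial's main motor measure, but MSEL fine motor is a primary outcome, the VABS-2 has a motor domain, and the same section lists further iPad parameters. A reader might also infer that unfamiliar words would make a child with better aim appear to get worse. Because the letters are displayed, the documents do not support that.

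**The data are recoverable.** All stimuli and responses are logged, so another rule can be applied later. That makes the correction cheap, but choosing the rule after seeing the data is weaker than stating it beforehand.

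**Conclusion.** The point holds for a secondary, exploratory measure. Under the natural reading of target key, the Type-mode rule combines symbolic key choice with aim, and the one stated filter separates child from caregiver, not right key from wrong key. A decline in wrong-letter presses would appear as motor improvement, and variation in them would inflate the iPad test-retest variance used for the full trial's sample size. Type-mode data matter because most children are expected to finish there.

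The direction is firm as long as wrong letters lie farther from the required key than ordinary aim scatter. The size is not known. On the assumed keyboard and scatter, a drop from 30% to 10% wrong letters gives a spurious fall of about 48% (even spread) or about 24% (adjacent keys). The trial's between-arm results and its other motor measures are unaffected.

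**What to change.** In the Internal iPad data section:

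1. State that the target key is the key of the required letter and, if pieces may be placed in any order, how that letter is determined.
2. Compute Type-mode motor targeting error from the child's own presses on or next to that key.
3. Report the proportion of presses landing farther away as a separate key-choice measure.
4. Keep the all-press distance as a sensitivity analysis.

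Distance to the nearest key should not be used. It is bounded, and it hides whole-key misses, which are informative in children selected for motor impairment.

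The cost is a few sentences and a derivation from contact data already logged; no new assessment is needed. There are two downsides. Very large motor misses move into the separate proportion, so that proportion is not purely symbolic. Wrong-letter choices on adjacent keys still count as motor error, so the correction helps little if most wrong presses fall there.

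### Motor efficiency is defined as unnormalised variance of linear and angular speed, so the index is confounded with how fast the child moves (and, for linear speed, how far)

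*Protocol article*

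**What the plan says.** The relevant text is in the protocol article, Secondary outcomes, Internal iPad data (the entry on finger movements, not the activity-log entry of the same name under the feasibility measures). The list of parameters opens with "Changes in manual motor skills will be measured by the following parameters". Its third item is that "motor efficiency is measured as variance of linear speed in the direction of motion, and variance of angular speed", with angular speed explained as "the rate of change in direction of motion over time". The fourth item, movement accuracy, is a ratio to the shortest possible path and is therefore already free of distance. The fifth includes a duration: "the overall time taken to successfully complete a piece are also recorded".

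The Statistical analysis plan section analyses logged measures of visuomotor accuracy in three exploratory analyses of covariance, "with Point OutWords usage time, number of distinct Point OutWords sessions, and real time as covariates". It also says that "Test-retest variances in internal iPad data and external outcome measures will be entered into a standard calculation of statistical power"; the purpose is to plan how large the full trial must be.

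The article does not say whether higher or lower variance means better efficiency, or whether variance is taken within a drag or across drags.

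**The concern.** A variance of speed carries the units of speed squared. It is small when everything happens slowly and large when everything happens quickly, whatever the smoothness of the movement. An intervention that trains manual motor skill through repeated practice may well make children faster. If it does, the third item in the list is pushed up by the same change that brings completion time, in the fifth item, down. Read with lower as better, the two would then point in opposite directions for a child who had simply improved.

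The planned covariates do not remove this. Usage time, number of sessions and real time describe the amount of exposure; none is the speed, length or duration of a drag. A gain in speed with practice would appear along those covariates as a trend in the index.

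Puzzle layout adds a second, smaller disturbance. The Intervention section describes pieces spread around the screen, so drags differ in length, and length alone moves the linear-speed part of the index.

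At stake is the interpretation of one named parameter of motor change and, through the power calculation, its suitability as a candidate measure for the full trial.

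**Working it through.** **Inputs.** The definition, the meaning of angular speed and the covariates come from the two sections cited above. The article gives no drag lengths, durations or speeds and no figure for this outcome, so there is nothing of its own to reproduce. All kinematic values below are assumptions for illustration.

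**Step 1: scaling, which needs no data.** Trace the same path c times faster. Linear speed v becomes c·v and angular speed w becomes c·w, so Var(v) and Var(w) are both multiplied by c². The ratio Var(v)/mean(v)² does not change.

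**Step 2: linear speed, smooth drag.** Assume a minimum-jerk profile of length D and duration T, with s = t/T: v = 30(D/T)(s² − 2s³ + s⁴). The mean is D/T, the variance is 0.4286(D/T)², and variance over squared mean is 0.4286 for any D and T.

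| D (cm) | T (s) | Var(v), cm²/s² | Var/mean² |
|---|---|---|---|
| 10 | 2 | 10.7 | 0.43 |
| 10 | 1 | 42.9 | 0.43 |
| 10 | 0.5 | 171.4 | 0.43 |
| 5 | 1 | 10.7 | 0.43 |
| 15 | 1 | 96.4 | 0.43 |

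The first three rows show the speed effect and the last two the distance effect at fixed duration. Smoothness is identical throughout.

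**Step 3: can the reading reverse when the child is also smoother?** Add a 4 Hz fluctuation to the 2 s drag. The variance is 15.2 with 50% fluctuation and 25.2 with 90%. The smooth 1 s drag scores 42.9, which is 42.9/25.2 = 1.7 to 42.9/15.2 = 2.8 times higher. Against the 90% case the reversal needs the smooth drag to take less than √(42.86/25.18) = 1.30 s. At 1.5 s the smooth drag scores 19.05 and is ranked correctly. So reversal is possible but not automatic.

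**Step 4: does the index respond to halting at all?** Take four 2.5 cm sub-movements, each lasting 0.7 s of a 1 s slot, so 10 cm in 4 s. The variance is 6.51, the mean speed 2.5, and variance over squared mean 6.51/6.25 = 1.04. Compress the same profile to 1 s: 6.51 × 4² = 104.1, against 42.9 for the smooth 1 s drag. At equal duration the order is right. At 4 s against 1 s it is wrong (6.5 against 42.9).

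**Step 5: angular speed.** Assume a sinusoidally curved path with deviation amplitude A.

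| T (s) | A | Var(w) | Var(w) × T² |
|---|---|---|---|
| 2 | 0.30 | 3.85 | 15.40 |
| 1 | 0.30 | 15.40 | 15.40 |
| 1 | 0.15 | 4.04 | 4.04 |
| 1 | 0.14 | 3.53 | 3.53 |

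The same path at double speed gives four times the variance. With the deviation halved to 0.15 the raw variance is still above the slow value (4.04 against 3.85); at 0.14 it falls below it. Multiplying by T² removes the speed effect and ranks the straighter path better in both cases. Changing only drag length, with shape and duration fixed, left Var(w) unchanged (6.60 at 5 cm and at 10 cm).

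**The case against.** The strongest reply is that the direction of scoring is not in the document. The article names efficiency, not smoothness, and never says that lower variance is better. It cites a pilot report for the recording, and a condensed article may leave normalisation and per-drag processing to fuller documents. The point about direction stands, and the conclusion is worded accordingly. It does not rescue the definition, because the opposite reading would score erratic movement as efficient. Nor is the formula merely left out: the article states it outright, and as stated it is unnormalised.

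A reader might infer that the index records only speed and distance and says nothing about smoothness. That is not supported: at equal duration the halting drag scores 104.1 against 42.9, so the index does respond to halting. A large contrast such as 6.5 against 42.9 rests on assumed and unequal durations. A reader might also infer that the distance effect and the reversal apply equally to angular speed. They do not: distance leaves angular-speed variance unchanged, and a sufficiently straighter path offsets the speed effect.

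The consequence is also limited. This is one parameter among several in a secondary outcome, and it is recorded only while Point OutWords is in use, so it gives no comparison between arms during the trial. The analysis of logged measures is exploratory and is described in terms of visuomotor accuracy. Completion time would make a change in speed visible. All of this lowers the weight of the point. It does not remove it, since change in the parameter is still to be read as change in motor skill and iPad-data variances are still to enter the power calculation.

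**Conclusion.** The point holds as a confounding of the index with movement speed, and for linear speed also with distance. The c² scaling for an unchanged path is an identity. For linear speed, a child who becomes faster with the same speed profile is certain to have a higher variance; if the child also becomes smoother, the reading may or may not reverse, depending on the size of each change. For angular speed, straightening of the path can cancel the effect.

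Recording such a child as less efficient requires the inference that lower variance is better. The documents do not show that children will speed up by any particular amount, so the figures illustrate size and do not predict a bias. The weight is moderate: a secondary, exploratory measure that is worth correcting because change in it is read as change in skill, because its variance may inform the full trial, and because the correction is cheap.

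**What to change.** In Secondary outcomes, Internal iPad data, replace the third parameter with two dimensionless quantities computed for each drag:

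- variance of linear speed divided by the squared mean speed of that drag;
- variance of angular speed multiplied by the squared duration of that drag.

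State that lower means smoother, and report mean drag speed alongside so that a gain in speed is shown as such. Turning per unit path length should not be used for the angular part: it has units of 1/length, and for the same shape it was 0.411 at 5 cm and 0.205 at 10 cm, so it would bring in a dependence on distance that angular-speed variance does not have.

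The cost is a change of formula on finger movements that are already logged, with no new data and no burden on families. One limitation remains. The normalised linear index does not detect stops without pauses: a 2 s drag broken into two, three or four full stops has the same variance (10.7) and the same mean as one smooth drag, so it also scores 0.43. The raw variance has the same blind spot. The index should therefore be read together with path ratio, failed attempts and completion time.
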